## Abstract

**Background:**

Patients with hypertension continue to have less than optimal blood pressure control, with nearly one in five Canadian adults having hypertension. Pharmacist prescribing is gaining favor as a potential clinically efficacious and cost-effective means to improve both access and quality of care. With Alberta being the first province in Canada to have independent prescribing by pharmacists, it offers a unique opportunity to evaluate outcomes in patients who are prescribed antihypertensive therapy by pharmacists.

**Methods:**

The study is a randomized controlled trial of enhanced pharmacist care, with the unit of randomization being the patient. Participants will be randomized to enhanced pharmacist care (patient identification, assessment, education, close follow-up, and prescribing/titration of antihypertensive medications) or usual care. Participants are patients in rural Alberta with undiagnosed/uncontrolled blood pressure, as defined by the Canadian Hypertension Education Program. The primary outcome is the change in systolic blood pressure between baseline and 24 weeks in the enhanced-care versus usual-care arms. There are also three substudies running in conjunction with the project examining different remuneration models, investigating patient knowledge, and assessing health-resource utilization amongst patients in each group.

**Discussion:**

To date, one-third of the required sample size has been recruited. There are 15 communities and 17 pharmacists actively screening, recruiting, and following patients. This study will provide high-level evidence regarding pharmacist prescribing.

**Trial Registration:**

Clinicaltrials.gov NCT00878566.

## Background

### The problem

Patients with hypertension continue to have less than optimal blood pressure control. Nearly one in five Canadians adults--about 4.6 million people between the ages of 20 and 79--have high blood pressure [1]. Almost 50% of patients between the ages of 60 and 79 had a diagnosis of hypertension, with the highest rates of hypertension in elderly women [1,2]. In the United States and Canada, approximately 50% and 35%, respectively, of patients with hypertension are not controlled. These numbers increase to over 60% in patients with diabetes [3,4]. Although awareness and control of hypertension have improved significantly in the last 20 years, there still is a large gap in care.

### The problem in rural communities

Care of patients with chronic diseases living in rural communities is sometimes difficult given the shortage of rural physicians and the lack of access to specialty care and other healthcare professionals. There is also evidence to suggest that practice guidelines may be implemented to a lesser extent in rural communities [5,6]. This provides an excellent opportunity for a multidisciplinary shared-care approach to screening, diagnosis, management, and follow-up of patients with hypertension [7].

### Pharmacists helping to solve the problem

There have been a number of interventions by pharmacists to help close these gaps in hypertension management [8,9]. In a recently published study on physician and pharmacist collaboration in a community medical office, there was an adjusted mean change in systolic blood pressure (SBP) of -12.0 mm Hg at six months and an absolute improvement in blood pressure (BP) control rates of 34% (from 30% in usual care to 64%) [10]. A systematic review conducted by the same group [11] investigated the effects of team-based care for hypertension. Pharmacist recommendations to the physician decreased overall SBP by 9 mm Hg.

In a recently completed study by our group, Improving blood pressure management in patients with diabetes study (SCRIP*-HTN*), a community pharmacist and nurse intervention (in which the treatment team monitored patients' blood pressures and faxed guideline-concordant treatment recommendations to their primary care physicians if they were above target) produced a 5.6 mm Hg greater decrease in SBP over 24 weeks compared to usual care in patients with diabetes and poorly controlled blood pressure [12]. Despite the improvement in mean blood pressure, only half of the patients reached their blood pressure goal. One potential explanation for this is that traditional pharmacist care can only go so far with recommending appropriate therapy (*i.e*., there is a ceiling effect based on whether or not the physician prescribes the recommended therapy).

As healthcare costs worldwide increase, pharmacist prescribing is gaining favor as a potentially clinically efficacious and cost-effective means to improve both access and quality of care [13]. Pharmacist prescribing is defined differently depending on the region; it can range from prescribing by protocol to independent prescribing. The Canadian province of Alberta has been a pioneer in the area of independent pharmacist prescribing by being the first jurisdiction in Canada to enact legislation for such. Pharmacists in Alberta now have the ability to apply for additional prescribing authorization. This authorization allows them to prescribe for minor self-limited or self-diagnosed conditions, to modify a prescription written by another prescriber, or to undertake comprehensive drug therapy management, which can include independent initiation of drug therapies [14].

Pharmacist prescribing is a relatively recent innovation, and as such, there is little evidence about its clinical or economic impacts. For instance, work in the United Kingdom has focused generally on attitudes towards pharmacist prescribing and on the value of training programs for pharmacist prescribing authority [15-17].

With Alberta being the first province in Canada to allow independent prescribing by pharmacists, it offers a unique opportunity to evaluate outcomes in patients who are prescribed antihypertensive therapy by pharmacists.

## Methods

### Study overview

The study is a randomized controlled trial of enhanced pharmacist care, with the unit of randomization being the patient. Participants are randomized to either enhanced pharmacist care (patient identification, assessment, education, close follow-up, and prescribing/titration of antihypertensive medications) or usual care (Figure 1). Due to the nature of the intervention, blinding of patients and practitioners is not possible, although outcomes will be adjudicated in a blinded fashion.

**Figure 1 F1:**
[figure not shown]
**Study Flow Diagram**. Flow diagram of randomization and follow-up of patients based on group assignment. Patients in enhanced care are followed up more closely until target blood pressure is reached. Patients randomized to usual care only have two follow-up visits. (HBPM = home blood pressure monitoring, q4 weeks = every 4 weeks, q3 months = every 3 months).

The primary objective is to evaluate the effect of enhanced pharmacist care on SBP in patients with poorly controlled hypertension in the rural setting. Secondary objectives include the number of patients at their BP target at 24 weeks, the number of new antihypertensive medication starts, the number of antihypertensive dosage changes (increases and decreases in dose), the number of antihypertensive medication changes, and the number of new prescriptions for aspirin and cholesterol medications.

### Patients

Participants are patients in rural Alberta with undiagnosed or uncontrolled BP as defined by the Canadian Hypertension Education Program (CHEP) [18]. Pharmacists screen patients using the criteria in Table 1, as adapted from the CHEP guidelines for the management of hypertension by pharmacists [19].

**Table 1 T1:** Screening parameters for pharmacists to identify potential participants

Screening Parameters	Details
Self-identified	

Screening days using validated devices	

Medication profiles	• Antidiabetes medications • Oral contraceptives • Antianginals • Antiplatelet agents • Cholesterol-lowering medications • Smoking cessation therapy • Treatments for erectile dysfunction

Patients with known cardio-, cerebro-, or peripheral vascular disease	

Patients with unfavorable cardiovascular risk factors	• Smokers • Overweight and obese • Increased age • Hyperlipidemia • Family history of cardiovascular disease

Referral from other healthcare professionals	

Patients are included if they meet one of the following criteria:

• Overall average (after two visits in undiagnosed patients without macrovascular target organ damage, diabetes [DM], or chronic kidney disease [CKD]) SBP ≥180 mm Hg or diastolic BP (DBP) ≥110 mm Hg

• Overall average (after two visits in patients with undiagnosed hypertension with macrovascular target organ damage) SBP ≥140 mm Hg or DBP ≥90 mm Hg

• An established diagnosis of hypertension above target BP, SBP ≥140 mm Hg (≥130 with DM or CKD), or DBP ≥90 mm Hg (≥80 with DM or CKD)

• Overall average (after five visits for those without macrovascular target organ damage, DM, or CKD and without an existing hypertension diagnosis) SBP ≥140 mm Hg or DBP ≥90 mm Hg

• Overall average (after seven days of twice-daily home BP monitoring for those without macrovascular target organ damage, DM, or CKD and without an existing hypertension diagnosis) SBP ≥135 mm Hg or DBP ≥85 mm Hg

These inclusion criteria are based on the CHEP criteria for the assessment of patients [18]. CKD is defined as patients with a glomerular filtration rate (as calculated by the Modification of Diet in Renal Disease equation) of < 60 mL/min for at least three months [20].

Patients are excluded if they are having a hypertensive urgency (defined as an SBP ≥200 mm Hg or DBP ≥130 mm Hg) or emergency, are unwilling to participate or sign the consent form, or if the patient is pregnant.

### Recruitment

Pharmacists actively screen for potential patients using the criteria in Table 1. Patients start by attending two screening visits, separated by two weeks. If their SBP is between 140-180 mm Hg and their DBP is between 90-110 mm Hg after the first two screening visits, they will be invited to either further evaluate their BP by home BP monitoring or have an additional three screening visits at the pharmacy. The home BP monitors will be lent to the patients by the pharmacists and are Canadian Hypertension Society approved devices.

### Randomization

After their screening is complete, patients will be invited to participate. Once the patient provides informed written consent, the participant is randomized (via a centralized secure website to ensure allocation concealment) in a 2:1 ratio to either enhanced pharmacist care or usual care (Figure 1) and enrolled by the pharmacist. The patients randomized to the enhanced pharmacist care group are further randomized to one of two payment structures for the pharmacist (fee for visit or payment for performance, Figure 2) in a 1:1 ratio. The randomization strategy employs variable blocked randomization stratified by study center.

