### Sample size and statistical analysis

Based on a two-sample, two-sided *t*-test, a sample size of 162 will provide 80% power to detect a minimally important clinical difference (MCID) of 8 mm Hg between intervention and usual-care groups, with a projected standard deviation of 18 in each group [12]. In the comparison of different payment models within the intervention arm, an alpha of 0.10 was used for a total of 224 patients to detect a 6 mm Hg MCID between the fee-for-visit group and the payment-for-performance group.

Assuming a drop-out or loss to follow-up rate of 10%, the sample size has been increased to 250 in the intervention group (125 in fee for service and 125 in payment for performance) and 90 in the usual-care group, for a total sample size of 340.

All analyses will be intention to treat. A comparison of baseline characteristics will be performed using *t*-tests or nonparametric Wilcoxon for continuous variables and chi-squared test for categorical variables. In order to account for any imbalance in baseline characteristics, the test for differences in change in SBP between intervention and usual-care groups will be adjusted for using multiple regression models (or analysis of covariance models). The problem of missing values will be checked for nonrandomness, and appropriate imputation methods will be applied when needed. All analyses will be carried out using SAS 9.1.3 (SAS Institute, Cary, NC, USA).

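### The 2:1 allocation and the planned arm sizes of 250 and 90 disagree; if 2:1 is applied to 340 patients, the payment comparison falls about 10 per group short of its own target

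*Protocol article*

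**What the plan says.** All references are to the protocol article.

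- **Randomization.** Patients are allocated "in a 2:1 ratio to either enhanced pharmacist care or usual care". Those in enhanced care are "further randomized to one of two payment structures for the pharmacist (fee for visit or payment for performance, Figure 2) in a 1:1 ratio". On method: "The randomization strategy employs variable blocked randomization stratified by study center".
- **Sample size and statistical analysis, primary comparison.** For a difference of 8 mm Hg, "a sample size of 162 will provide 80% power", "with a projected standard deviation of 18 in each group". No alpha is given for this comparison.
- **Same section, payment comparison.** Here "an alpha of 0.10 was used for a total of 224 patients to detect a 6 mm Hg MCID". Neither a power nor an SD is repeated for it.
- **Same section, after allowing for 10% loss.** The plan is "250 in the intervention group (125 in fee for service and 125 in payment for performance) and 90 in the usual-care group", which the article sums to 340.

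No text in the article connects the 2:1 ratio with these arm sizes. The two flow diagrams could not be seen for this check.

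**The concern.** The ratio and the arm sizes are both stated as facts of the design, and they differ: 250/90 = 2.78. Chance imbalance is not a credible explanation, because blocking within centre holds the realised ratio close to the nominal one.

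The payment comparison is exposed because it determines the size of the enhanced-care arm. If patients are allocated 2:1 and recruitment stops at 340, that arm ends about 23 short of 250, and the comparison does not reach the 224 evaluable patients set for it. A reader also cannot tell which power figures describe the trial being run.

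**Working it through.** **Inputs.** From the sample size section: 8 mm Hg with 162 patients, 80% power and SD 18 (primary); 6 mm Hg with 224 patients and alpha 0.10 (payment); 10% loss; 250 + 90 = 340. From the Randomization section: 2:1, then 1:1 within enhanced care. Assumed: two-sided alpha 0.05 for the primary comparison; SD 18, a two-sided test and 80% power for the payment comparison.

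**Step 1. Reproduce the article's own figures.** For two equal groups, n per group = 2 × SD² × (z for alpha + z for power)² / difference².

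- Payment: 2 × 324 × (1.645 + 0.842)² / 36 = 111.3, so 112 per group and 224 in total. This matches exactly, and the exact t calculation gives 223.9. A one-sided test at 0.10 would give 164, which does not match.
- Primary: 2 × 324 × (1.960 + 0.842)² / 64 = 79.5, so 80 per group. The exact t calculation gives 80.4, so 81 per group and 162 in total, as stated.
- Loss: 112/0.9 = 124.4, so 125 per payment group and 250 in enhanced care; 81/0.9 = 90 in usual care.

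The arm sizes are therefore consistent with two separate equal-group calculations: the payment comparison gives the enhanced-care arm, and half of the primary sample gives the usual-care arm. The 2:1 ratio plays no part in them.

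**Step 2. Apply 2:1 to 340.** 340 × 2/3 = 226.7 and 340/3 = 113.3, so about 227 and 113. Even under simple, unblocked 2:1 randomisation, the binomial probability of 250 or more of 340 in enhanced care is about 0.004. Blocking makes it smaller still.

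**Step 3. Apply 10% loss.** 226.7 × 0.9 = 204 and 113.3 × 0.9 = 102. Enhanced care splits into 102 per payment group. Under 250:90 the same step gives 225 and 81, or 112.5 per payment group.

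**Step 4. Payment comparison, 6 mm Hg, alpha 0.10.**

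- 102 per group: standard error 18 × √(2/102) = 2.52; 6/2.52 − 1.645 = 0.736; power 76.9% (exact t 76.7%).
- 112.5 per group: standard error 18 × √(2/112.5) = 2.40; 6/2.40 − 1.645 = 0.855; power 80.4% (exact t 80.2%).
- Difference detectable with 80% power at 102 per group: (1.645 + 0.842) × 2.52 = 6.3 mm Hg.

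**Step 5. Primary comparison, 8 mm Hg, alpha 0.05.**

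- 204 against 102: standard error 18 × √(1/204 + 1/102) = 2.18; 8/2.18 − 1.960 = 1.71; power 95.6% (exact t 95.5%).
- 225 against 81: standard error 18 × √(1/225 + 1/81) = 2.33; 8/2.33 − 1.960 = 1.47; power 92.9% (exact t 92.8%).

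**Step 6. Sensitivity of the payment power under 2:1 at 340** (normal approximation).

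| Condition | Power |
|---|---|
| SD 17, 10% loss | 80.9% |
| SD 18, 10% loss | 76.9% |
| SD 19, 10% loss | 72.9% |
| SD 18, no loss (113 per group) | 80.6% |

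Of the SDs tried (16 to 20 in whole units), only 18 gives 224 at 80% power.

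**The case against.** The strongest reply is that only the contradiction is established, not the power loss. The article does not show which statement is the slip. If the arm sizes are right, payment power is about 80% and nothing is lost. The same is true if recruitment under 2:1 runs on until 250 patients are in enhanced care. The 80% target and SD 18 are inferred for the payment comparison, and an SD one unit higher costs as much power as the mismatch does. This stands: the 77% is conditional and should be quoted with its conditions.

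It is also fair that the consequence is small and falls on a substudy. The main comparison gains slightly from 2:1, and no estimate is biased. This stands too, and limits the weight of the point.

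A reader might go further and infer that the primary comparison is mis-sized, because 162 is an equal-groups figure and the trial does not use equal groups. The article does not support that. The 162 serves to set a minimum of 81 evaluable patients in the smaller arm, the payment comparison then enlarges the other arm, and either allocation of 340 gives well over 80%. Nobody proposes randomising 162 patients 2:1, so the power of such a design is beside the point.

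None of this removes the disagreement between the two sections.

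**Conclusion.** The point holds as an internal contradiction that should be fixed: 2:1 in centre-stratified blocks and 250:90 cannot both describe a 340-patient trial.

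Its size is conditional. If 2:1 is the operating ratio, the total stays at 340 and loss is 10%, the payment comparison has about 77% power for 6 mm Hg, roughly 3 points below its apparent target. This takes SD 18, two-sided alpha 0.10 and an 80% target for that comparison, an inference supported by the exact match to 224. A flat statement that the comparison has 77% power would be too strong, since the article leaves open which section is correct. The trial's primary conclusion is not threatened.

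**What to change.** Confirm which ratio the central randomisation system uses, then make the Randomization and sample size sections agree.

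- **If it is 2:1 with 340 patients:** restate the sample size section as about 227 in enhanced care (113 or 114 per payment group) and 113 in usual care. Give primary power of about 95% for 8 mm Hg and payment power of about 77% for 6 mm Hg, or 6.3 mm Hg at 80%. This is wording only; one power figure becomes slightly less favourable.
- **If the system implements the stated arm sizes:** correct the ratio in the Randomization section to the one actually used, and give about 93% primary and about 80% payment power. Also wording only. The ratio should be taken from the system and not back-calculated: an exact 25:9 needs blocks of at least 34, while 340 patients over 15 sites average about 23 per site.
- **If both 2:1 and 250 in enhanced care are to be kept:** usual care must be 125 and the total 375. This costs 35 more patients, and payment power is then about 80%.

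In each case, state the alpha for the primary comparison and the SD and power assumed for the payment comparison. The article reports one-third of the sample recruited, so the check can still be made during recruitment.

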### Setting

Pharmacists and pharmacies are selected based on their current practice model, size, and location of the community (population of < 20,000 and located more than one-hour driving distance from Edmonton and Calgary) and willingness to apply for additional prescribing authorization.

Currently we have 15 sites involved in the study, with two sites that have multiple pharmacists participating. The majority of sites are community pharmacies, but sites also include pharmacists in primary care networks and hospital-based pharmacists who provide some outpatient services. All study data are collected in the pharmacy and faxed to the study office using unique patient identifiers to conceal the identity of the patients.

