### Study status

To date, one-third of the required sample size has been recruited. There are 15 sites and 17 pharmacists actively screening, recruiting, and following patients.

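### Randomisation is stratified by study centre, but the stated reason for adjusting the SBP comparison would not normally bring centre into the model; fixing centre in advance is a small, free improvement

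*Protocol article*

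**What the plan says.** All of this is in the Protocol article.

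- **Randomization.** Patients are allocated "in a 2:1 ratio to either enhanced pharmacist care or usual care". A second step follows: "The patients randomized to the enhanced pharmacist care group are further randomized to one of two payment structures for the pharmacist", in equal numbers. The section closes with "The randomization strategy employs variable blocked randomization stratified by study center".
- **Study status.** "There are 15 sites and 17 pharmacists actively screening, recruiting, and following patients". The Setting section adds that there are 15 sites, "with two sites that have multiple pharmacists participating". Centre and pharmacist therefore nearly coincide.
- **Sample size and statistical analysis.** The main comparison is sized on a simple t-test of two group means, with no centre term: "a sample size of 162 will provide 80% power to detect a minimally important clinical difference (MCID) of 8 mm Hg". The SD is taken as 18 per arm. The payment comparison uses an alpha of 0.10, 224 patients and a 6 mm Hg difference. The target is 250 + 90 = 340 after allowing for 10% loss.
- **Same section, analysis.** Baseline characteristics are to be compared by significance tests. The test of SBP change "will be adjusted for using multiple regression models (or analysis of covariance models", and the purpose given is to deal with baseline imbalance. No covariate list follows. Neither centre nor pharmacist is mentioned as a covariate, stratum or random effect.

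**The concern.** A stratification factor belongs in the analysis because the randomisation was restricted on it, whether or not the arms turn out balanced. The article gives a different reason for adjusting, namely observed imbalance. Blocking within centre makes centre about the last variable that such a check would flag, so the stated rationale points away from the one factor that the design calls for.

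If centre is left out and centres differ in mean SBP change, the arm difference is estimated more precisely than the model reports. The between-centre spread stays in the residual variance although stratification has removed it from the comparison. The confidence interval is then too wide and a little power is lost. The same logic applies to the payment comparison if its 1:1 allocation is also blocked within centre.

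**Working it through.** **Inputs from the article:** 15 sites; 2:1 allocation; SD 18 mm Hg; difference 8 mm Hg; total 340; 10% loss, so 340 × 0.9 = 306 completers. **Assumed:** two-sided alpha of 0.05 for the main comparison (not stated); ICC of SBP change by centre 0.01 to 0.20; SD of the treatment effect between centres 2 to 6 mm Hg. The article gives neither of the last two.

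**1. Reproduce the stated figure.** n per arm = 2 × 18² × (1.96 + 0.842)² / 8² ≈ 79.5, so 80 per arm and 160 in total. The exact t calculation needs 81 per arm, total 162, with 80.3% power. The stated 162 is reproduced for equal arms with no centre term. The payment figure of 224 also reproduces (112 per arm, alpha 0.10).

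**2. Centre left out, same effect in every centre.** With arms balanced within centre, the reported SE exceeds the true one by about 1/√(1 − ICC). True type I error = 2 × [1 − Φ(1.96/√(1 − ICC))]. This was checked by simulation: 6,000 runs per scenario, 15 unequal centres, exact 2:1 blocks and 306 completers, for which the SE without centre effects is 18 × √(1/204 + 1/102) = 2.18.

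| ICC | SE factor, formula | Type I, formula | Mean SE without / with centre, simulated | Type I without / with centre, simulated | Power at 8 mm Hg without / with centre |
|---|---|---|---|---|---|
| 0.01 | 1.005 | 4.9% | 2.178 / 2.168 | 4.9% / 5.0% | 95.4% / 95.5% |
| 0.05 | 1.026 | 4.4% | 2.176 / 2.126 | 4.5% / 4.9% | 95.8% / 96.2% |
| 0.10 | 1.054 | 3.9% | 2.168 / 2.068 | 4.3% / 5.2% | 96.4% / 97.2% |
| 0.20 | 1.118 | 2.8% | 2.156 / 1.950 | 3.0% / 4.8% | 97.5% / 98.6% |

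Monte Carlo error on a 5% rate is √(0.05 × 0.95/6000) ≈ 0.3 points. For ICC 0.01 to 0.10 the power loss is 0.1 to 0.8 points; at 0.20 it is 1.1 points.

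The simulation uses 2:1. The stated group sizes of 250 and 90 leave 225 and 81 completers, with SE 18 × √(1/225 + 1/81) = 2.33 and power of about 93%. The SE factor depends on the ICC and not on the split.

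**3. Payment comparison.** If its allocation is also blocked within centre, the same factor applies. At alpha 0.10, 2 × [1 − Φ(1.645 × factor)] gives 9.8%, 9.2% and 8.3% for ICC 0.01, 0.05 and 0.10. This was worked by formula only, not simulated.

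**4. Effect varying between centres (separate question).** Simulated with ICC 0.05. Type I error here concerns a mean effect of zero over a wider population of pharmacists.

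| SD of effect (mm Hg) | No centre term | Centre fixed effect | Centre-clustered SE | Power at 8 mm Hg, clustered SE |
|---|---|---|---|---|
| 2 | 5.3% | 6.0% | 6.0% | 91% |
| 4 | 8.1% | 9.0% | 6.0% | 86% |
| 6 | 12.2% | 13.8% | 6.8% | 76% |

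A centre main effect does not remove this excess and slightly raises it. Clustered SEs remove most of it, but stay somewhat above 5% with 15 centres, which is why small-sample degrees of freedom are needed.

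**The case against.** The strongest reply is that the article is a condensed account and leaves the covariates open. Imbalance is offered as a motive for adjusting, not as a closed selection rule, and an analysis plan that is not shown may well name centre. This stands as far as it goes: a reader might infer that centre is excluded from the analysis, and the text does not say so. What remains is not the missing list. It is that the one rationale given is the wrong basis for a stratification factor.

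A reader might also infer that the planned standard errors are invalid, or that false positives follow. Omitting centre works in the other direction. Nor is the primary comparison a plain t-test: that test appears for sizing the trial and for comparing baseline characteristics, while SBP change is tested in a regression or ANCOVA model.

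A third tempting reading is that variation between pharmacists makes the primary test anti-conservative. The article gives no SD for that variation and does not state whether the target is the effect in these pharmacists or in pharmacists generally. For the participating pharmacists the usual SE is adequate. The inflated rates in the second table also need a null under which some pharmacists lower SBP, others raise it, and the average is exactly zero. This reading supports a sensitivity analysis and no more.

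**Conclusion.** The point holds in a limited form. The design restricts allocation by centre, while the stated ground for adjustment would not normally select centre, and the article neither includes nor excludes it. If centre were omitted, the cost would be an SE about 0.5% to 5% too large, a true type I error of roughly 4% to 5%, and under 1 point of power. These figures are conditional on an assumed ICC of 0.01 to 0.10 and an assumed alpha of 0.05. No conclusion of the trial is threatened, and the main comparison remains well powered. The case for changing the text is that the better analysis costs nothing.

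**What to change.** State in the analysis section, or in the analysis plan before results are seen, that the SBP models for both the main and the payment comparison include study centre (fixed effect or random intercept) and baseline SBP, whatever balance is observed.

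Add one sensitivity analysis for the main comparison: a random treatment-by-centre effect with small-sample degrees of freedom. Present it as addressing inference beyond the participating pharmacists.

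The cost is wording only. Centre is already known for every patient through the stratified randomisation, and the article reports one-third of the sample recruited, so the change could be made without knowledge of outcomes. Neither the sample size nor the data collection changes.
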